### 2.5. Randomization and Blinding

The volunteers will be randomly assigned to one of the three arms: low-frequency WBV (16–26 Hz) associated with ST (G1), WBV sham associated with ST (G2), and an untreated group (G3). A researcher not involved in the study will perform the volunteers’ randomization using the webpage www.randomization.com (accessed on 20 January 2018). and subsequently, their allocation will be through opaque, sealed, sequentially numbered envelopes assigned to the interventions management team. 

The envelopes will be opened, in order, by the intervention team that will reveal the type of treatment to be assigned to the volunteers.

The study nature will prevent blinding of the intervention team and volunteers. However, the researcher that conducts the initial and final assessment of the outcomes and the statistician will be blinded to the allocation.

### 2.6. Intervention

The training protocol will last for 12 weeks (3 months) and comprise three times a week for 60 min each session. Before each session, the volunteers in arms G1 and G2 will be instructed by the intervention team to perform basic warming and stretching exercises accordingly to the Ramos protocol [21]. 

The ST consists of two sets (A and B) each to be performed alternately [39,40], as shown in Table 1, in accordance with recommendations of the American College of Sports Medicine (ACSM) for older adults [41] and Brazilian Diabetes Society (Sociedade Brasileira de Diabetes—SBD) [9]. A frequency of three days a week will be applied, very light to light intensity (40% to 50% of the test of a maximum repetition—1RM) and seven exercises involving the main muscle groups. In the 1RM test, a familiarization will be performed (pre-session), starting with 10% of body weight, progressing to the maximum lifting capacity, for a maximum of 5 attempts with an interval of 30 s between each attempt. The test will be performed bilaterally, starting with the nondominant side [42].

In addition, dumbbells and grounded muscle training equipment with different loads (Mega II, Marca Movement) will be used. The training will start initially with two sets of eight repetitions (1st to 4th week), progressing to two sets of twelve repetitions (5th to 8th week) and, finally, two sets of fifteen repetitions (9th to 12th week) [9,41]. The rest between sets will be sixty seconds and the load will gradually increase according to a good exercise performance. The strength training protocol will be applied to arms G1 and G2 equally.

Next, WBV will be applied through the Kikos P204–110v platform (Kikos Fitness, São Paulo-SP, Brasil), which has an oscillatory lateral vibration direction. The vibrating platform baseplate is slip-resistant for better safety during the training [7]. The amplitude (the vertical displacement of oscillatory motion) will be determined by the distance between both feet on the surface of the platform, ranging from approximately 2.0 mm to 5.0 mm [43]. A gradual increased in vibration frequency (the number of cycles of oscillation) and exposure duration was performed to avoid an early muscle activity decrease [44,45,46]. Vibration frequency and time spent between use and rest per week are described in Table 2.

On the platform, barefoot volunteers will adopt an isometric squat positioning at 40°, verified with a conventional goniometer. On their heels, silicon insole will be applied (semi-rigid) in order to keep only the forefoot and middle-foot in direct contact with the platform surface, thus correcting the body weight distribution and foot biomechanics changes. Both strategies will be used to minimize the axial transmission to cranial base [7,21,47]. In accordance with the International Organization for Standardization (ISO) 2631-1, all the parameters are considered safe for body exposure to mechanical vibration [48].

The WBV sham (simulation) will be performed with the platform unplugged. A speaker connected to the platform will emit a similar sound during the time equivalent to the protocol, since the vibrating stimulus cannot be visually differentiated. The volunteers that experience the simulation will have to adopt the same squat positioning during the session. We will assure no contact between volunteers from arms G1 and G2 [47].

The volunteers in arm G3 group will be instructed to manage their diabetes as usual routine without practicing physical activity. All of them will be informed that they will be scheduled to receive the treatment after 12 weeks. 

It is worth mentioning that the entire intervention team will be submitted to a complete 8 h training. 

### 2.7. Outcome Measurements

#### 2.7.1. Primary Outcomes

**Skin temperature**

The thermographic imaging of lower limbs will be captured by FLIR E40bx^®^ camera (FLIR^®^ Company, Wilsonville, Oregon, EUA), with thermal sensibility of 0.5 °C, light emission value of 0.987 and 160 × 120 pixels resolution. The camera will be positioned at a distance of 1 m from the regions of interest with a 90° angle (perpendicular) relative to the camera lens [49].

The volunteers will have fifteen minutes for acclimatization and rest as the body temperature comes into alignment with the room temperature. The test room temperature will be controlled at 18 °C and 23 °C with relative air humidity between 40 and 70% monitored with a precise thermo hygrometer (KT-908). All volunteers will be previously oriented to avoid pain killers or vasoactive drugs, lotions or moisturizing creams on the regions of interest, in addition to caffeine and nicotine in the 4 h before the exam [49].

After the acclimatization period, the thermal images of the interest points will be registered and, subsequently, the mean temperature will be analyzed by the thermographic software provided by the manufacturer (FLIR^®^ Tools). Table 3 shows the six regions of interest [50]. All the photographic images will be collected by one evaluator only with expertise in managing the camera.

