### 2.4. Sample Size

The sample size was based on the primary outcome of lower-limb blood flow circulation evaluated by infrared thermographic imaging (ITI). A minimal clinically important difference for skin temperature asymmetry on the knee anterior region is over 0.5 °C [37]. Based on data from a pilot study, two proportions were compared (G1 = 40% and G3 = 10%), considering power of 80% to detect differences between groups and 5% level of significance. The following formula was used:n = [(Z*α*/2 + Zβ)^2^ P(1 − P)]/(P − Po)^2^

According to the calculation in [38], a sample of approximately 15 volunteers per arm would be necessary. We expect a realistic drop-out rate of about 20%; therefore, 17 volunteers are estimated to be enrolled in each group (total of 51 volunteers).

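### The test room may sit anywhere from 18 to 23 °C and need not match between a volunteer's two visits, which adds avoidable noise to the absolute skin temperature that is analysed

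*Protocol article*

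**What the plan says.** Section 2.7.1 (Skin temperature) specifies how the thermal images are taken.

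- **Camera:** described "with thermal sensibility of 0.5 °C", with 160 × 120 pixels, at a fixed distance and angle.
- **Room:** "The test room temperature will be controlled at 18 °C and 23 °C", with humidity kept in a stated range and monitored.
- **Acclimatization:** "The volunteers will have fifteen minutes for acclimatization and rest". The protocol explains that body temperature comes to match the room during this time.
- **Operator:** "All the photographic images will be collected by one evaluator only with expertise in managing the camera".
- **Variable:** "the mean temperature will be analyzed by the thermographic software provided by the manufacturer". "Table 3 shows the six regions of interest", and these are thigh, leg and foot regions, two views each. There is no separate knee region.

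Section 2.4 sizes the trial on thermography and cites one important difference: "A minimal clinically important difference for skin temperature asymmetry on the knee anterior region is over 0.5 °C". Section 2.9 compares continuous variables within groups by paired t-test and between groups by ANOVA (or nonparametric tests). It names no adjustment for room temperature.

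**The concern.** Read as a range, the room rule is 5 °C wide. Nothing ties a volunteer's second visit to the room temperature of the first, so one volunteer could be imaged at 18 °C at baseline and 23 °C at 12 weeks, or the reverse, and still be within protocol. By the protocol's own account of acclimatization, the body adjusts towards the room, so part of that difference can appear as a change in skin temperature.

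A left-right difference would be largely protected, because a shift common to both limbs subtracts out. The mean temperature of a region is not. Averaging more pixels does not help either, because the whole image shifts together. What is at stake is precision in the outcome on which the trial was sized, with 17 volunteers enrolled per arm and about 15 expected to be evaluable.

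Two figures in the same sections also need attention. The stated camera sensitivity equals the cited threshold of 0.5 °C. And that threshold belongs to a different quantity (knee asymmetry) from the one measured.

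**Working it through.** There is no plan figure to reproduce here: the protocol gives no SD for skin temperature, no measurement error and no skin-to-room slope.

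**Inputs from the protocol**
- Room band 18 to 23 °C, width 23 − 18 = 5 °C (section 2.7.1).
- Two visits, baseline and 12 weeks.
- About 15 evaluable and 17 enrolled per arm (section 2.4).
- 5% significance level (section 2.9).

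**Assumptions, not in the documents**
- Skin temperature moves k = 0.1 to 0.4 °C per 1 °C of room temperature.
- Room temperature is uniform over the allowed band and independent between the two visits.
- The SD of the pre-post change without any room effect is 0.5 or 1.0 °C.

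**Step 1. Noise added to the pre-post change**

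SD of the room at one visit = width/√12 = 5/√12 = 1.44 °C. SD of the difference between two visits = 1.44 × √2 = 2.04 °C. Added SD = k × 2.04. For a room held within ±1 °C the width is 2 °C, which gives 2/√12 × √2 = 0.82 °C, and the added SD = k × 0.82.

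| k | Added SD, 18–23 °C | Added SD, ±1 °C | Largest possible shift, 18–23 °C (5k) |
|---|---|---|---|
| 0.1 | 0.20 | 0.08 | 0.5 |
| 0.2 | 0.41 | 0.16 | 1.0 |
| 0.3 | 0.61 | 0.24 | 1.5 |
| 0.4 | 0.82 | 0.33 | 2.0 |

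The last column is reached only when the two visits fall at opposite ends of the band.

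**Step 2. What this does to a comparison of two arms**

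Total SD = √(SD² + added SD²). Power is for a two-sample t-test, two-sided 5%, 15 per arm, and a difference in change of 0.5 °C. That difference is used only for illustration, because the protocol states no important difference for mean temperature.

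| k | SD 0.5: 18–23 °C | SD 0.5: ±1 °C | SD 1.0: 18–23 °C | SD 1.0: ±1 °C |
|---|---|---|---|---|
| no room effect | 0.75 | 0.75 | 0.26 | 0.26 |
| 0.1 | 0.69 | 0.74 | 0.25 | 0.26 |
| 0.2 | 0.54 | 0.71 | 0.23 | 0.26 |
| 0.3 | 0.39 | 0.66 | 0.20 | 0.25 |
| 0.4 | 0.28 | 0.60 | 0.18 | 0.24 |

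Example, k = 0.3 and SD 0.5: total SD = √(0.25 + 0.375) = 0.79 °C over the full band, against √(0.25 + 0.06) = 0.56 °C within ±1 °C. The loss is large if the underlying change varies little. It is small if it varies a lot, because power is then poor already.

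**Step 3. The camera figure**

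If 0.5 °C is independent noise per pixel, a mean over 100 pixels has an error of 0.5/√100 = 0.05 °C, which is negligible. If instead it is the error SD of each regional mean, a left-right difference has an error SD of 0.5 × √2 = 0.71 °C, and a person with no true asymmetry exceeds 0.5 °C in absolute value with probability 0.48. The documents do not say which reading applies.

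**The case against.** The strongest reply is that the room noise is assumed, not shown. The slope is not in the documents. The room is said to be controlled and monitored, so actual temperatures may vary far less than a uniform spread over 5 °C. The protocol also has real safeguards: acclimatization, a humidity range, fixed distance and angle, restrictions before the exam and a single evaluator. With random allocation and a blinded assessor (section 2.5), room differences should fall evenly across arms, so they add noise, not bias, unless visit conditions happen to differ by arm. All of this stands, and it limits the size of the point. None of it removes the point, because no listed safeguard ties the two visits to one room temperature.

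A reader might go further and infer that a camera with a stated sensitivity of 0.5 °C cannot reliably resolve a 0.5 °C effect. The documents do not support that. Sensitivity is not the error of a mean over many pixels, and a group mean can be estimated more finely than a single reading; step 3 shows that the consequence runs from negligible to serious. Nor is 0.5 °C the target effect for the measured variable, since it is cited for knee asymmetry. For the same reason, the room shifts should not be expressed as multiples of it.

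Two other inferences also go too far. Thermography is the basis of the sample size, but the protocol lists three primary outcomes without ranking them. And although Doppler, TUG and the pressure platform use the mean of three measures, the lack of a stated image count for thermography is silence in a condensed article, not a defect. Repeat images in one sitting would not remove a room difference between visits in any case.

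**Conclusion.** The point holds as a cheap improvement in precision. As written, the room rule can add an SD of 0.20 to 0.82 °C to the pre-post change in regional mean temperature, against 0.08 to 0.33 °C with the room within ±1 °C. Both ranges rest on the assumed slope of 0.1 to 0.4 and on room temperature uniform over the band and independent between visits; if the room is in practice steadier than the band allows, the gain is smaller. The effect is on precision, in thermography only. Doppler velocity and TUG are not touched by this calculation.

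The camera figure is a matter for verification: it may be a reporting slip or may mean something other than the error of a regional mean. The mismatch between a knee-asymmetry threshold and mean temperature in thigh, leg and foot regions is plain from the text, and it leaves the analysed variable without a stated important difference.

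**What to change.** 1. In section 2.7.1, name one room set-point inside 18 to 23 °C, hold it within about ±1 °C, and require the same set-point at both visits of a volunteer. Record the actual room temperature at each imaging session.
2. Check the stated 0.5 °C sensitivity against the camera's specification. Correct it if needed, and say what it measures.
3. Do not use the 0.5 °C knee-asymmetry threshold to interpret mean temperature in the six regions. Either give an important difference for the variable that is analysed, or state that none is available.

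The cost is somewhat tighter climate control and an occasional rescheduled visit when the room is out of range. The two text changes cost nothing. No change to sample size, equipment or treatment is involved.

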**Mean peripheral arterial blood flow velocity**

Mean dorsal pedal and posterior tibial arteries blood flow velocity will be measured by a handheld Doppler ultrasound (RH-BV-620VP, Guangdong, China/Mainland) with continuous sinusoidal wave emission. The skin site for the test will be coated with a water-soluble gel, and the high-frequency (8.0 MHz ± 10%) transducer will be placed at a 45° angle in relation to the blood vessel analyzed (against the flow) [44]. For measurements related to the dorsal artery of the foot and posterior tibial artery, foot dorso and distal third of the calf will be the area of reference, respectively. The volunteers will be positioned seated with supported feet and the confirmation of the most adequate site will be performed based on the audible signals generated by the Doppler device. The measurements will be expressed in centimeter per second (cm/s), using the mean of three measures of each artery with a 60 s interval [51]. All examinations will be performed by the same experienced examiner.

**Mobility**

Functional mobility will be tested by Timed Up and Go test (TUG), which is a rapid test and sensible for detecting changes in older adults. It consists of standing up from an armless chair, walking 3 m away to a marked post, turning 180 degrees, and walking back to the chair and sitting down without support. The chair to be used has a seat height of 45 cm. Older adults without functional mobility deficit are able to complete the test in less than 10 s [52]. It will be performed three times with 30 s intervals and the result considered will be the mean of performance timed by a stopwatch (Oregon Scientific, Portland, OR, USA, model SL-210).

#### 2.7.2. Secondary Outcomes

**Quasi-static posture**

An optoelectronic system BTS SMART DX100 (BTS Bioengineering, Milan, Italy) with four cameras equipped with 850 nm LED illuminators sensible to infrared (resolution 640 × 480) will be used to measure body alignment from the lower limbs. Before capturing data, a calibration process (static and dynamic) will be performed for spatial accuracy in reconstructing the three-dimensional model from this horizontal (x and y) and vertical (z) coordinate system. The maximum error of spatial positioning reconstruction is 0.5 mm [53].

After collecting the anthropometric data (height, weight, distance between anterosuperior iliac spines, lower limbs length and pelvic cavity depth), twenty-two reflective markers (15 mm of diameter) will be attached with double sided-tape on anatomical reference sites in accordance with Davis model (Figure 2) [54].

All volunteers will be invited to stand in a marked spot, keeping a rest position with arms extended by their side for a 10 s registration period. After capturing and reconstructing the 3D model, data will be imported and processed by SMART-Clinic^®^ software. From the anatomical points referenced, the following will be evaluated: pelvic obliquity (PO), pelvic tilt (PT), pelvic rotation (PR), hip ad/abduction (HA), hip flexion/extension (HF), hip rotation (HR), knee valgus–varus (KV), knee flexion/extension (KF), knee rotation (KR), ankle plantar/dorsiflexion (AP) and foot rotation (FR) [54].

**Plantar pressure and body balance**

MPS Biomech^®^ Baropodometric Modular Platform (LorAn Engineering, Bolonha, Itália) with 50–100 Hz acquisition and compatible with software Studio BIOMECH^®^ (Letsense group) will be used to determine plantar pressure and body balance in open-eyed (OE) and close-eyed (CE) conditions.

The barefoot volunteers will be instructed to stand in the middle of the platform, with a loose and habitual posture, bipodal stance and arms extended along their body. The volunteer will be asked to keep eyes directed to the fixed point in front of them in order to control possible changes in the visual field under OE condition [55]. Before capturing data, a 30 s adaptation period will be allowed. Each record will last for 20 s and it will be invalidated in cases of the participant moving or unbalancing, which will require the acquisition process to be repeated. The mean of three measures will be used for data analysis.

The evaluation of plantar pressure, bilaterally, will consider maximum and mean pressures, contact area and mean percentage of weight distribution. To measure the balance, the following variables will be analyzed: center of pressure displacement (COP), COP velocity, anteroposterior displacement (X axis) and mediolateral displacement (Y axis).

### 2.8. Monitoring Measurements

**Vital signs and capillary glycemia**

Before and right after each session, systolic (SBP) and diastolic (DBP) blood pressure will be measured by an aneroid sphygmomanometer and a stethoscope (Premium, China), and will be classified according to the recommendations from the Brazilian Society of Cardiology [56].

The number of breaths per minute (RR) will be registered by the chest movement or abdominal compartment for a 60 s period, and the heart rate (FR) and peripheral oxygen saturation (SpO2) will be measured by a portable pulse oximeter (More Fitness, MF-416, China) [57]. 

Capillary glycemia will be monitored by a portable blood glucose meter (ACCU-CHEK^®^ Active, Roche Diabetes Care, model GU) in accordance with the parameters recommended by ISO 15197:2013 [58].

**Other biochemical markers**

In the initial assessment and in the reassessment after 12 weeks, glycated hemoglobin (HbA1c) and lipid-related cardiovascular risk factors (total cholesterol, triglycerides, high density lipoprotein—HDL, low density lipoprotein—LDL and very low density lipoprotein—VLDL) will be analyzed [20].

### 2.9. Data Processing and Analysis

All data records will be kept under custody of LACIRTEM lab and an allocation-blind statistician will conduct all analysis using Statistical Package for the Social Science (SPSS, IBM^®^, EUA), version 23.0, with 5% (*p* < 0.05) level of significance.

Sociodemographic, anthropometric and baseline clinical data for both groups will be expressed as the mean and standard deviation for continuous variables, proportions and percentages for nominal variables. The Kruskal–Wallis H test will be used for continuous variables and Chi-square test will be used to associate nominal variables in order to verify homogeneity between baseline data among the groups. 

All analysis will be conducted in accordance with the intention-to-treat method (ITT) using the last observation carried forward (LOCF) method, which inputs baseline data at postintervention for the dropout cases [59]. Missing values due to participants’ nonattendance or withdrawal are expected in clinical trials. Continuous variables with normal distribution will be expressed as mean and standard deviation and the intra-group comparison will be performed by paired *t*-test, and the inter-group comparison by analysis of variance (ANOVA). For nonnormal continuous variables, data will be expressed in median and interquartile intervals (Q25–Q75) and compared within the groups by Wilcoxon test and among the groups by Kruskal–Wallis H test. Size effect will be calculated to support the statistical significance. 

We will also investigate and register the possible adverse events during the treatment protocol. 

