## Abstract

Vascular endothelium insults caused by high serum glucose levels affect the oxygen supply to tissues, via the microvascular endothelium, resulting in an increased perfusion heterogeneity. These insults may lead to the underuse of blood capillaries, while other vessels are overused and effectively overload their oxygen supply capacity, which eventually causes damages to distal parts of the peripheral nervous system. Therefore, the proprioceptive and exteroceptive feedback information will be gradually lost and contribute to a mobility reduction. This study aims to assess the efficacy of whole-body vibration (WBV) associated with strength training (ST) on lower-limb blood flow and mobility in older adults with type 2 diabetes (DM2). Methods and analyses: This is a protocol (1st version) for Pa single-blind, randomized, controlled clinical trial guided by the SPIRIT guidelines. Our sample will consist of 51 older adults with DM2 randomly allocated to three groups: low frequency WBV (16–26 Hz) associated to ST (G1), WBV sham (G2) and nonintervention control (G3). The study protocol is set for a 12-week (three times per week) schedule. Primary outcomes: skin temperature using infrared thermographic imaging (ITI); mean peripheral arterial blood flow velocity (MBF) by a handheld Doppler ultrasound (DU), and functional mobility by Timed Up and Go (TUG) test. Secondary outcomes: quasi-static posture using the DX100 BTS Smart optoelectronic system, and plantar pressure and body balance using the MPS stabilometric platform. Data will be collected and analyzed at baseline and post-intervention, considering *p*-value < 0.05 level of significance. The analyses will also be conducted with an intention-to-treat method and effect size. Dissemination: All results will be published in peer-reviewed journals as well as presented in conferences.

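### The stated LOCF is baseline carried forward: it scores every drop-out as zero change, shrinks effects under equal loss, and can bias arm comparisons under unequal loss

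*Protocol article*

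**What the plan says.** Section 2.9 sets the analysis principle: "All analysis will be conducted in accordance with the intention-to-treat method (ITT"). The same sentence names the missing-data method, the "last observation carried forward (LOCF) method, which inputs baseline data at postintervention for the dropout cases". It adds that "Missing values due to participants’ nonattendance or withdrawal are expected in clinical trials". No other method and no sensitivity analysis for missing data is named.

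The Abstract gives two measurement times: "Data will be collected and analyzed at baseline and post-intervention". Section 2.5 agrees, referring to "the researcher that conducts the initial and final assessment of the outcomes". Section 2.4 states: "We expect a realistic drop-out rate of about 20" per cent, with 17 volunteers enrolled per arm. No drop-out rate by arm is given.

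The between-arm test in section 2.9 is ANOVA, or Kruskal–Wallis for non-normal variables. The text does not say whether it is applied to 12-week values or to changes.

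**The concern.** With one post-baseline visit, the last observation of anyone who misses it is the baseline. The rule therefore asserts that no drop-out changed at all, and it analyses that assertion as data. It applies to all three primary outcomes.

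Zero change is a strong claim in this trial. Section 2.6 gives G1 and G2 the same strength training, which the Introduction expects to benefit vascular function. The hypothesis concerns what vibration adds to that training, so G1 vs G2 is the contrast that answers it. If both arms improve because of the shared training but lose different numbers of people, the rule pulls their means down by different amounts.

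Unequal loss is possible. Section 2.5 says volunteers cannot be blinded. G3 attends no sessions and is promised treatment afterwards, while G1 and G2 attend three times a week for 12 weeks. At stake are the size of each primary estimate and, under some patterns of loss, the false-positive rate.

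**Working it through.** The plan gives no figure for the effect of its missing-data rule, so there is none to reproduce.

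**Inputs from the protocol article.** Two outcome visits (Abstract, 2.5); baseline entered for drop-outs (2.9); about 20% drop-out and 17 per arm (2.4); 5% significance level and ANOVA between arms (2.9); strength training common to G1 and G2 (2.6).

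**Assumed, not in the document.** Outcome SD 1, baseline-to-12-week correlation 0.7, size of any mean change, drop-out share by arm, and drop-out unrelated to outcome.

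**Step 1: general bias.** Let d1 and d2 be the drop-out shares in two arms, and D1 and D2 the mean changes that the drop-outs would have shown. Replacing those changes by zero removes d × D from each arm's mean change. The bias in arm 1 minus arm 2 is

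bias = d2·D2 − d1·D1.

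**Step 2: drop-outs like completers.** With arm mean changes Δ1 and Δ2, the expected estimate is

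Δ1(1 − d1) − Δ2(1 − d2).

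At d1 = d2 = 0.20 this is 0.80 × (Δ1 − Δ2), so a true 1.0 SD is estimated as 0.80 SD. Simulation (20,000 runs) gave 0.80, against 1.00 from observed cases. With whole people, 3 of 17 lost gives 14/17 = 0.82.

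Power also falls. With true changes of 1, 0.5 and 0 SD and 3 of 17 lost per arm (4,000 runs), ANOVA power was 49% against 60% for observed cases on 12-week values, and 81% against 84% on changes.

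**Step 3: same true change, unequal loss.** With Δ1 = Δ2 = Δ, the expected false difference is Δ(d2 − d1):

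- Δ = 1, loss 30% vs 10%: 1 × (0.10 − 0.30) = −0.20 SD.
- Δ = 0.5, same loss: 0.5 × (−0.20) = −0.10 SD.
- Δ = 1, loss 35% vs 5%: 1 × (−0.30) = −0.30 SD.
- Δ = 0, any loss: 0.

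**Step 4: type I error by simulation.** 17 per arm, third arm losing 20%, all three arms sharing the same change, 20,000 runs per row. Each ANOVA entry gives 12-week values, then changes.

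| Common change | Loss | Three-arm ANOVA | Pairwise change-score t-test |
|---|---|---|---|
| 0 | 30% vs 10% | 4.9%, 5.4% | 4.9% |
| 0.5 SD | 30% vs 10% | 5.5%, 6.3% | 7.0% |
| 1 SD | 30% vs 10% | 7.0%, 9.4% | 11.4% |
| 1 SD | 35% vs 5% | 9.7%, 15.1% | 19.6% |

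Observed-case analysis stayed near 5% in every row.

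**Step 5: the contrast of interest.** Let only G1 and G2 change, each by 0.8 SD, with 1 of 17 and 5 of 17 lost. The expected false G1–G2 difference is 0.8 × 4/17 = 0.19 SD (simulated 0.18 to 0.19). The G1–G2 t-test rejected in 7 to 10% of runs, against 5 to 6% for observed cases.

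**The case against.** Four objections have weight.

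**The false-positive rates depend on invented inputs.** A reader might infer that the trial will run at 11 to 20% type I error. The document does not support that. It gives no common change and no drop-out by arm. The higher figures need a 1 SD shift and a pairwise change-score t-test, whereas section 2.9 names ANOVA. Drift from room or season is a weak source for such a shift: section 2.7.1 controls room temperature and humidity and allows acclimatisation, and with staggered enrolment season could move people in different directions. The shared strength-training response is a better-grounded source. This objection stands on size.

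**Carrying baseline forward may be reasonable or cautious.** Someone who leaves early may keep little benefit. If drop-outs would truly not have changed, Step 1 gives no bias, and under equal loss with drop-outs like completers the rule shrinks towards the null. So it is not always anti-conservative. Nor is it reliably conservative. With 20% loss in both arms, if G1 drop-outs would not have changed and G2 drop-outs would have gained 0.5 SD, the bias is 0.20 × 0.5 − 0.20 × 0 = +0.10 SD in favour of G1. Also, observed cases hold 5% here only because drop-out was simulated as unrelated to outcome.

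**Clinical size cannot be read off section 2.4.** It is tempting to set a false difference of 0.20 against the 0.5 °C given there. That figure is a threshold for temperature asymmetry at the anterior knee, not for a between-arm difference in mean change. Nor can one say that planned confidence intervals are too narrow, because section 2.9 mentions none.

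**A second analysis may exist.** The Abstract says that intention-to-treat analyses will be done as well, which hints at another analysis set. It describes no other handling of missing values, so the stated rule remains the only one.

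**Conclusion.** The point holds as a defect in a stated rule, not as an omission. Baseline carried forward is the only missing-data method given, it covers all analyses, and it treats an assumed zero change as observed.

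The firmest figure is the shrinkage: a factor of 0.80 at equal 20% loss, provided drop-outs would have changed like completers. The false difference under unequal loss is mean change times difference in drop-out share, and it vanishes when there is no mean change. The resulting type I error is modest in the moderate scenarios: about 6 to 9% with the three-arm ANOVA and 7 to 11% with a pairwise change-score t-test at 30% vs 10% loss and a common change of 0.5 to 1 SD. It reaches 10 to 15% and 20% respectively only at 35% vs 5% loss and 1 SD. All of these rest on the assumed correlation, mean change and loss by arm. Bias in the estimates is the larger worry. The change should be made; the design is not affected.

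**What to change.** In section 2.9, replace LOCF for the primary analysis with a likelihood-based model of the baseline and 12-week values of all randomised participants, for example SPSS MIXED with arm, visit and arm-by-visit terms. SPSS is already the named software. Everyone with a baseline value stays in the analysis, which keeps the intention-to-treat aim, and no value is invented. The model is valid when drop-out depends only on observed data, and the text should state that assumption. Keep baseline carried forward as a labelled sensitivity analysis, and report drop-out by arm beside it.

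Multiple imputation within arm with several predictors is not advised as the main method: at 20% loss, about 14 people per arm would be observed (17 × 0.80 = 13.6), too few for a stable imputation model.

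The cost is a change of analysis wording, slightly more analysis work, and a somewhat larger standard error, because drop-outs no longer count as fully observed. The model takes the place of the planned ANOVA as the primary between-arm comparison, so the protocol needs to say so.
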